### Statistical analysis

Data exploration using descriptive statistical analysis and inferential statistics is performed. The sample data is carried out by frequencies or percentages, means and standard deviation, and graphics. 95% confidence intervals (CI) are calculated for the differences in percentages and medians. T-test and chi-square test is used to compare groups at baseline. Moreover, Pearson’s- and Spearman’s correlation coefficients is used. In order to test the normal distribution, histograms and box plots will be applied. If normal distributions are not met, non-parametric tests such as Wilcoxon, Mann–Whitney-U-Test and Kendall’s tau and Spearman’s correlation coefficients are chosen. Analysis of covariance (ANCOVA), comparing parameters after the intervention (AP2) and after the follow-ups (AP3, AP4) between intervention and control group, adjusting for the baseline value as covariate is performed. The IBM® SPSS® Statistics for Windows, Version 20 software (IBM Corp., Armonk, NY, U.S.) is used for all statistical analyses. All tests are two-sided and a p-value <0.05 is considered statistically significant.

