### Sample size calculation

For sample size calculation, the difference in handgrip strength from the first assessment point (AP1) to the second assessment point (AP2), which take place 10–12 weeks after AP1 (see Figure 
1), is considered as a marker of muscle strength. We examine its relationship with diet
[24,33] and physical activity
[34] in a community-dwelling cohort. Given a clinically relevant difference of 2 kg in handgrip strength (intervention group improves by 2 kg more than the control group in handgrip strength), a standard deviation of 3 kg of the differences, a two-sided significance level of 0.05, a sample size of n = 36 per group is needed to reach 80% statistical power. Since imputation for drop-outs may have some inestimable effect on the assumed standard deviation of the differences, the sample size is increased to n = 40 per group. Expected value μ1 (intervention) = 16 kg, μ2 (control) = 14 kg (based on the results of the pre-study
[42,44]). The primary endpoint is analyzed according to the intention-to-treat principle (ITT).

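### No test is named as primary, and an uncriterioned visual normality check can be read as deciding whether baseline-adjusted ANCOVA or an unadjusted rank test settles the handgrip result

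*Protocol article*

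**What the plan says.** All references are to the protocol article.

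The Statistical analysis section runs in this order:

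1. Descriptive statistics, with this sentence on intervals: "95% confidence intervals (CI) are calculated for the differences in percentages and medians".
2. T-test and chi-square for baseline comparisons, then Pearson and Spearman correlations.
3. Histograms and box plots to check normality.
4. The switch rule: "If normal distributions are not met, non-parametric tests such as Wilcoxon", followed by Mann-Whitney, Kendall and Spearman.
5. ANCOVA comparing the arms at AP2, AP3 and AP4, "adjusting for the baseline value as covariate is performed".

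None of these is called the primary analysis.

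The Sample size calculation section sizes the trial on "the difference in handgrip strength from the first assessment point (AP1) to the second assessment point (AP2". Its inputs are: "Given a clinically relevant difference of 2 kg in handgrip strength", "a standard deviation of 3 kg of the differences" and "a two-sided significance level of 0.05". It concludes that "a sample size of n = 36 per group is needed to reach 80% statistical power", raised to 40 per group. It also lists expected values of 16 kg and 14 kg, and says that the primary endpoint is analysed by intention to treat.

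**The concern.** The switch rule is stated in general terms. It relies on a look at plots, has no threshold, and does not say whether raw values, changes or residuals are plotted. ANCOVA needs roughly normal residuals, not normal raw values, so the choice of plot matters. Mann-Whitney is a between-arm test, and nothing keeps the rule away from the primary endpoint. A reader can therefore take the rule to mean that the outcome data decide which test settles handgrip strength.

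Two things would be at stake. First, the deciding test would be chosen by judgement after the data are seen. Second, a plain rank test has no baseline covariate. If it were run on AP2 values it would drop the baseline information altogether.

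The interval sentence adds a mismatch that does not depend on how the rule is read. The trial is sized on a 2 kg mean difference and ANCOVA estimates an adjusted mean difference, but the intervals promised are for percentages and medians.

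**Working it through.** **Inputs from the article:** difference 2 kg, SD of the AP1 to AP2 differences 3 kg, two-sided 0.05, 80% power, 36 per group raised to 40.

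**Assumption (not in the article):** baseline-to-AP2 correlation ρ from 0.5 to 0.9, with equal SD at both times.

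**Step 1, the plan's own figure.** n = 2(1.96 + 0.842)² × 3²/2² = 35.3, so 36 per group. This reproduces the stated number. (With the noncentral t, power at 36 is 79.7%.)

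**Step 2, t-test on change at n = 40.** Power = Φ(δ/(SD√(2/n)) − 1.96). Here 2/(3 × √(2/40)) = 2.98, so power = Φ(1.02) = 84.6%.

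**Step 3, SDs implied by a change SD of 3 kg.**
- Raw SD at AP2: 3/√(2(1 − ρ)).
- ANCOVA residual SD: raw SD × √(1 − ρ²).
- Mann-Whitney: same power formula with n × 3/π = 38.2 per arm (its relative efficiency under normality).

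Example at ρ = 0.8: raw SD = 3/√0.4 = 4.74 and residual SD = 4.74 × 0.6 = 2.85. Mann-Whitney on raw AP2: 2/(4.74 × √(2/38.2)) = 1.84, so power = Φ(−0.12) = 45%.

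**Step 4, results at 40 per arm.** Each cell gives the formula value, then a simulation with normal data (20,000 runs).

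| ρ | Raw SD (kg) | ANCOVA residual SD (kg) | ANCOVA | Rank test on change | Rank test on raw AP2 |
|---|---|---|---|---|---|
| 0.5 | 3.00 | 2.60 | 93% / 92% | 83% / 81% | 83% / 81% |
| 0.7 | 3.87 | 2.77 | 90% / 89% | 83% / 81% | 62% / 60% |
| 0.8 | 4.74 | 2.85 | 88% / 87% | 83% / 82% | 45% / 44% |
| 0.9 | 6.71 | 2.92 | 86% / 85% | 83% / 81% | 26% / 24% |

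By the formula, a rank test on change costs about 2 points against the t-test on change, and 3 to 10 points against ANCOVA. A rank test on raw AP2 values costs about 10 points at ρ = 0.5 and about 60 at ρ = 0.9.

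**Step 5, a bound on the type I error.** If one simply took whichever of ANCOVA and the raw-AP2 rank test was significant, the simulated error (4,000 runs) would be 6.7% at ρ = 0.5, rising to 8.9% at ρ = 0.9, instead of 5%. That is free choice between the two tests. A choice made from plots would be less extreme.

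**The case against.** The best defence is the order of the text. The rank methods listed are the usual counterparts of the t-tests and correlations named just before them. The ANCOVA comes afterwards in its own sentence, with no condition. On that reading ANCOVA is always done and the baseline adjustment is never lost. This stands as a plausible reading, and the article nowhere says that ANCOVA is replaced. But it does not confine the rule to the earlier tests either, nor say which result counts if ANCOVA and a rank test disagree.

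The second defence is that the sized endpoint is the change from AP1 to AP2. A rank test on that variable still uses the baseline and stays above the 80% target. This also stands. The rule does not name the variable, however. The ANCOVA sentence compares values at AP2, and the listed 16 kg and 14 kg look like levels, so a substituted rank test could fall on AP2 values.

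Third, the figures above assume normal data, while the rule would act on data judged non-normal. That is a real limit: the table shows what dropping the baseline costs, not the power in the situation that triggers the switch.

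Fourth, a condensed article may leave the interval for the ANCOVA contrast, and the stratum in secondary models, to a fuller plan. This is fair for the stratum, which is only a minor addition here. The main point is not an omission: the article states the switch rule and leaves its scope open.

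**Conclusion.** The point holds as an ambiguity in a stated rule. The article leaves open whether ANCOVA or an unadjusted rank test decides the handgrip result, and makes that depend on an uncriterioned look at plots. The power cost runs from a few points (rank test on change) to half or more (rank test on raw AP2 values with ρ of about 0.8 or higher). Which of these applies rests on a reading that the text does not settle and on a correlation that it does not give.

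A reader might infer more, and the article does not support it:

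- **That the rule roughly halves power.** This needs both the raw-AP2 reading and the high correlation.
- **That the switch is likely to happen**, because handgrip pooled over men and women looks skewed or bimodal. The article gives no handgrip distribution and no sex mix.
- **That a switch leaves no estimate in kg.** An interval for a difference in medians is planned, and for handgrip it would be in kg. It is simply not an interval for the mean difference.
- **That a switch loses the precision on which the sample size relies.** The calculation uses the SD of the differences, not ANCOVA.

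This should be corrected before analysis. It does not show that the planned size is wrong.

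**What to change.** - Name ANCOVA of AP2 handgrip on arm and AP1 handgrip as the single primary analysis, whatever the plots show.
- Report the adjusted mean difference in kg with a 95% interval. If the residuals are clearly non-normal, use a bootstrap or robust interval for the same estimate.
- Keep rank tests on handgrip as sensitivity analyses only, and say which variable they use.
- State which tests the normality rule governs, and extend the interval sentence to the adjusted mean difference.
- Add the handgrip randomisation stratum to the ANCOVAs of the other outcomes. The handgrip model already contains the stratifying variable as its baseline covariate. Sex as a further covariate is optional.

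The cost is wording in the protocol or analysis plan. No extra participants, visits or data are needed.

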### Recruitment and eligibility

#### Malnourished frail persons

Malnourished frail people 65 years and older, who are inpatient in five hospitals in Vienna, wards for internal medicine, and close to discharge are recruited in four waves within one year. The inclusion and exclusion criteria for malnourished frail persons are shown in Table 
1.

**Table 1 T1:** Inclusion and exclusion criteria of frail malnourished persons

**Inclusion criteria**	**Exclusion criteria**
▪65 years or older	▪Planned admission to nursing home
▪Resident in Vienna	▪Chemo or radiotherapy at the moment or planned
▪Malnutrition or at risk of malnutrition according to the MNA-SF (≤ 11 points) OR	▪Nursing level 6^a^ or 7^b^
Frail or pre-frail according to the SHARE-FI (female: >0.315; male: >1.212 points)	
▪Community-dwelling	▪Insulin treated diabetes mellitus according to the medical charts
▪No medical contraindication for the performance of strength training (“No” to the question ‘Has your doctor recently told you that you should not exercise?”)	▪COPD stage III or IV
▪Able to walk (with or without a walking aid)	▪Dialysis patient or chronic kidney insufficiency with protein restriction
▪Capability to consent	▪Cannot understand the German language
	▪Impaired cognitive function according to the MMSE (≤ 17 points)

^a^more than 180 hours of care is necessary; care cannot be planned or is permanently required.

^b^more than 180 hours of care is necessary; person cannot move without help.

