### Randomization

Persons are randomly assigned to the intervention or control group, stratified by handgrip strength with the help of the “Randomizer for Clinical Trials 1.8.1″
[45]. Randomization is carried out after the patient has signed the informed consent and has been matched to a lay buddy, dependent on the place of residence.

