• *Quality of life* assessed by the World Health Organization Quality of Life WHOQOL-BREF
[49] and by 3 dimensions of the WHOQOL-OLD (“sensory functions”, “autonomy”, “activities in the past, present and future”)
[50]

• *Social support* measured with the short version of the questionnaire F-SozU
[51].

• *Frequency of hospitalization*

• *Frequency of falls*

• *Documentation of fear of falling* assessed by the FES-I (Falls Efficacy Scale-International Version)
[52]

Measurements of frailty, nutritional status, physical activity:

• *Frailty status* assessed by the SHARE-FI (Frailty Instrument for Primary Care of the Survey of Health, Ageing and Retirement in Europe)
[3]. According to the results of the SHARE-FI, persons are categorized in frail, pre-frail, and robust people divided by gender. The handgrip strength, which is the primary endpoint of the study and part of the SHARE-FI, is measured with a hydraulic dynamometer in standardized procedure
[53]. For each side three attempts are made, and the highest one is used for calculation.

• *Nutritional status* assessed by the long form of the MNA (Mini Nutritional Assessment)
[54]. In our study calf circumference is used which is measured with a tape at the sitting patient on the left and the right lower leg at the strongest circumference
[55]. Different to the protocol, persons put their feet on the floor while measuring.

• *Cognitive function* assessed by the German version
[56] of the MMSE (Mini Mental State Examination)
[57].

• *Body mass index (BMI; kg/m*^
*2*
^*)* while body height is assessed by a yardstick and body weight by a calibrated scale.

• *Body composition* assessed by the BIA (Bioelectrical Impedance Analysis) in standardized procedure
[58]. Moreover, waist circumference is measured at a vertical level 2.5 cm above the umbilicus while expiration
[59].

• *Quality of the diet* assessed by the Mediterranean Diet Adherence Screener (MEDIAS)
[60], a food frequency questionnaire assessing the protein intake and questions concerning supplements
[61].

• *Qualitative and quantitative contents of refrigerators* assessed by a predefined protocol and picture of refrigerator
[62].

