• *Muscle strength* assessed by the MASS (Measurement of age and sex related reference values of muscle strength) and the Concept 2 Dyno. The MASS is a new diagnosis system which was developed by the Technical University of Vienna. It evaluates health related concentric dynamic muscle strength. The measurement is velocity-independent and hence, is appropriate for the target group. Three exercises (bench press, bench pull, and leg press) will be conducted in standardized procedure. For all tested muscle groups the following parameters are recorded: maximum resistance with low velocity and 2–3 fix adjusted sub-maximum loads. Moreover, the Concept 2 Dyno is used for assessing the muscle strength. The same exercises as before will be conducted in standardized procedure
[63].

• *Daily physical activity* assessed by an activity sensor (pedometer), the modified PASE (Physical Activity Scale for the elderly)
[64] and the modified questionnaire on health-related behavior FEG (Fragebogen zur Erfassung des Gesundheitsverhaltens)
[65]. The pedometer-data will be analyzed as follows: Data from the week before AP2, AP3 and AP4 will be included in the analysis. Data of those who have used the pedometer less than four days are excluded. Days, on which the pedometer was used less than eight hours, are considered as invalid. The number of steps below 90 steps per minute, the number of steps above 90 steps per minutes and the walk time is analyzed.

• *Balance and mobility components* assessed by the SPPB (Short Physical Performance Battery)
[66].

• *Laboratory parameters* for malnutrition or frailty (albumin, total cholesterol, transferrin, triglyceride, 25-hydroxy-vitamin D, folic acid, CRP, IL-6, TNF-alpha and leucocytes)

Other measurements

• *Personal data* e.g. age, gender, family status, education level, income, occupation

• *Measures of drop-out (DO)*[67]*:* the drop-out rate between the first and second visit and until the final visit should be analyzed. For each case of discontinued participation (Ri), the following reasons are discriminated: medical reason (R1) and person’s own decision (R2), whereas an “A” stands for all participants who passed the baseline assessment.

• Drop-outs between the first and second visit:

⋅DO_R_ = DO_1_ + DO_2_ – all participants who drop out between the first and second visit

⋅DO_R1_ = DO_1_/A – percentage of participants who discontinue by medical reasons.

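### The handgrip ANCOVA names only the baseline value as covariate; prespecifying sex as well may add a little precision for one degree of freedom

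*Protocol article*

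**What the plan says.** The Statistical analysis section compares the arms at AP2, AP3 and AP4 by ANCOVA, "adjusting for the baseline value as covariate". No further covariate is named. The Measurements section identifies the primary endpoint: "The handgrip strength, which is the primary endpoint of the study and part of the SHARE-FI, is measured with a hydraulic dynamometer".

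Four other places bear on sex:

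- Sex is collected. The personal data are listed as "e.g. age, gender, family status, education level, income, occupation", and Table 3 places personal information at AP1.
- Table 1 admits both sexes and gives separate SHARE-FI thresholds, "female: >0.315; male: >1.212 points". The Measurements section also forms the SHARE-FI categories by gender.
- One strength instrument, MASS, is named "Measurement of age and sex related reference values of muscle strength".
- The Randomization section allocates persons "stratified by handgrip strength". Sex is not named as a stratification factor.

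The Sample size calculation uses a 2 kg difference in change, an SD of 3 kg for the change and a two-sided 0.05 level. It finds 36 per group for 80% power and raises this to 40.

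**The concern.** Men and women enter one model with a single baseline slope. If the sexes differ in mean handgrip, a man and a woman with the same AP1 value have different expected AP2 values, because each tends to regress toward the mean of their own sex. A model with baseline alone gives them the same prediction, and the difference goes into the residual. Adding the stratifying variable does not cure this, since handgrip is already in the model for the primary endpoint.

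What is at stake is some residual variance in a comparison of 40 persons per arm. Sex is already recorded, so removing that variance needs no new data. Naming sex in advance also closes off a later choice about whether to adjust, should the arms turn out to differ by sex.

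**Working it through.** **The plan's own figure.** With a difference of 2 kg, SD 3 kg, two-sided 0.05 and 80% power, n per group = 2 × [3 × (1.960 + 0.842) / 2]², which rounds up to 36. The stated figure is reproduced (a t-based calculation gives 37). At 40 per group the standard error is 3 × √(2/40) = 0.671 kg and power is Φ(2/0.671 − 1.960) = 84.6%. This uses the SD of the change and takes no credit for any covariate.

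**Inputs for the check.** From the article: SD of change 3 kg, difference 2 kg, 40 per arm. Assumed, because the article does not give them: within-sex SD of handgrip s = 4-6 kg, mean male-female gap D = 5-10 kg, share of men p = 25-45%, and the same mean change in both sexes.

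**Formulas.**

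- An SD of change of 3 fixes the within-sex AP1-AP2 correlation: r = 1 − 9/(2s²).
- Between-sex variance: B = p(1 − p)D². Total variance: T = B + s².
- Residual variance, baseline only: V₀ = T − (B + r s²)²/T.
- Residual variance, baseline and sex: V₁ = s²(1 − r²).
- Sex coefficient given baseline: (1 − r)D. It is not zero when D is not zero and r is below 1.
- Power (normal approximation): Φ(2/√(V × 2/40) − 1.960).

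**Worked example, s = 5, D = 8, p = 0.35.** r = 1 − 9/50 = 0.82. B = 0.2275 × 64 = 14.56 and T = 39.56. V₀ = 39.56 − (14.56 + 20.5)²/39.56 = 8.49. V₁ = 25 × (1 − 0.6724) = 8.19. The variance falls by 0.30/8.49 = 3.5%. The sex coefficient is 0.18 × 8 = 1.44 kg.

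| s (kg) | D (kg) | men | V₀ | V₁ | variance fall | power, baseline only | power, with sex |
|---|---|---|---|---|---|---|---|
| 6 | 5 | 25% | 8.50 | 8.44 | 0.8% | 86.6% | 86.8% |
| 6 | 8 | 35% | 8.60 | 8.44 | 1.9% | 86.2% | 86.8% |
| 5 | 8 | 35% | 8.49 | 8.19 | 3.5% | 86.7% | 87.8% |
| 4 | 8 | 35% | 8.34 | 7.73 | 7.2% | 87.2% | 89.5% |
| 4 | 10 | 45% | 8.50 | 7.73 | 9.0% | 86.6% | 89.5% |

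A t-based calculation lowers the powers slightly (86.4% and 88.8% in the fourth row) and leaves the differences about the same.

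**Simulation.** This used 4000 trials per setting, allocation stratified at the median of handgrip and 35% men. Power without and with sex was:

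- s = 4, D = 8: 84.9% and 87.3%
- s = 5, D = 8: 85.0% and 86.0%
- s = 5, D = 10: 84.4% and 85.6%
- s = 5, D = 5: 86.2% and 86.5%

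Other runs at 35% men gave changes of −0.2 to +1.5 points. Where sex was assumed to add nothing once baseline is known, power fell slightly, for example from 84.1% to 83.3%. The mean estimate was about 2.0 kg, the true value, with and without sex.

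**Chance imbalance.** Handgrip-stratified allocation still left a sex imbalance between arms with an SD of 8-10 percentage points. The part that matters is what baseline handgrip does not already account for. Its effect on the estimate has SD √[(V₀ − V₁) × 2/40]:

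- s = 5, D = 8: √(0.30 × 0.05) = 0.12 kg
- s = 4, D = 8: √(0.60 × 0.05) = 0.17 kg

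In the simulations the two estimates from one trial differed with an SD of 0.12-0.19 kg. In the s = 5 case the squared standard error is 8.49 × 0.05 = 0.424 without sex and 8.19 × 0.05 = 0.410 with it. The gap of about 0.015 is the 0.12 kg squared. Imbalance and lost precision are therefore the same quantity.

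**The case against.** The strongest case against is that nothing here is an error. ANCOVA on the outcome's own baseline is valid under randomisation, and for handgrip the covariate is also the stratifying variable, so design and model agree. The article does not say that baseline is the sole covariate, and a fuller list could stand in an analysis plan that is not shown. The cited places show at most that levels differ by sex; none says that sex predicts AP2 handgrip once AP1 is known. The SD, gap and share of men are all assumed.

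Most of this stands. It limits the point to an optional gain whose size the article cannot settle. Two things remain. The article does state a specific adjustment, so the suggestion alters a stated choice and does not fill a silence. And with a 3 kg SD of change the within-sex correlation is below 1, so under equal mean change any sex gap in handgrip leaves a nonzero sex coefficient given baseline.

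A reader might infer that omitting sex biases the treatment effect, or that chance imbalance is a second harm beside lost precision. Neither is supported: the estimate averages the true 2 kg either way, and the imbalance is random error that the standard error already includes.

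**Conclusion.** The point holds as a small, optional improvement to the primary handgrip analysis. Under the stated assumptions the residual variance falls by about 1-9% and power changes by about 0-3 percentage points. There is no gain in the weakest settings, and a slight loss if sex has no association with AP2 handgrip given baseline. The shift of about 0.1-0.2 kg in a single trial compares with a standard error of about 0.65 kg. The sample size of 36, raised to 40, does not depend on this.

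It is tempting to extend the argument to body composition or to add age on the same ground. The article gives no basis for the first, and no calculation supports the second. For frailty, the SHARE-FI categories are already formed by sex, which weakens the case there.

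**What to change.** For the primary comparison of handgrip at AP2, specify ANCOVA adjusting for baseline handgrip and sex, and record this before outcome data are analysed. Keep the model with baseline alone as a sensitivity analysis, so that the result under the published wording can still be read. The cost is one phrase in the analysis section and one degree of freedom; no new data, visits or participants are needed.
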